## Abstract

**Background:**

In recent years, behavioral therapy with comprehensive behavioral intervention for tics (CBIT) has been recognized as an effective and safe treatment in patients with Gilles de la Tourette syndrome. In Germany, however, dissemination of CBIT is restricted due to a considerable lack of well-trained therapists. The aim of this study is to overcome this deficiency by creating a new and sophisticated Internet-delivered CBIT (iCBIT) program. With this study, we want to demonstrate that iCBIT is superior to Internet-delivered psychoeducation and comparable to face-to-face CBIT.

**Method and analysis:**

This is a multicenter, prospective, randomized, controlled, observer-blind clinical trial, which will be conducted at five sites in Germany (ONLINE-TICS). Over the course of 2 years, 160 adult patients with chronic tic disorders will be assigned to one of three treatment arms: iCBIT (*n* = 72), online psychoeducation (*n* = 72), or face-to-face CBIT (*n* = 16). All treatments will consist of eighty therapy sessions over a period of 10 weeks and will follow the well-established CBIT manual by Woods and colleagues. The primary outcome measure will be the change in Yale Global Tic Severity Scale (YGTSS) at 1-week posttreatment. Secondary outcome measures include YGTSS change at 3 and 6 months, video- and self-ratings of tics as well as scales for psychiatric comorbidities assessed at each visit. The primary analysis will compare iCBIT to online psychoeducation using a mixed linear model with the YGTSS change as dependent variable. Secondary analyses will look at the comparison between iCBIT and face-to-face CBIT in a non-inferiority analysis.

**Discussion:**

If iCBIT proves to be effective, it would be a considerable contribution to close the wide gap in treatment providers for tic disorders not only in Germany but also in several other countries, since this Internet-delivered therapy does not require the supervision of a therapist. In addition, iCBIT would be a cost-effective and readily available treatment alternative that guarantees high quality standard of CBIT.

**Ethics and dissemination:**

All institutional review boards approve the protocol. All participants will provide informed consent. There are no conflicts of interest. After study completion, the results will be published.

**Study registration:**

ClinicalTrials.gov Identifier: NCT02413216.

## Introduction

Gilles de la Tourette syndrome (TS) is a chronic neuropsychiatric disorder of childhood onset characterized by multiple motor and vocal tics. While tics are described and diagnosed phenotypically, there is pathophysiological evidence for an involvement of cortico-striato-thalamo-cortical circuits. Tic disorders are common with a prevalence of 0.4–3.8% (1). The majority of patients additionally suffers from comorbidities such as attention deficit hyperactivity disorder (ADHD), obsessive-compulsive disorder (OCD), depression, anxiety, and self-injurious behavior (2). Quality of life is significantly impaired in a substantial number of patients not only due to tics and comorbidities but also because of ignorance and a lack of information, leading to bullying and stigmatization. Even today, it takes on average more than 5 years to make the correct diagnosis (3). According to a recent German study, TS is a cost-intensive disease that causes high direct and in particular high indirect costs (average total annual disease specific costs in Germany = €3404) including indirect medical costs for productivity loss of €2511 ± 3810 and for absenteeism of €260 ± 1184 (4). Thus, TS poses a considerable burden not only to patients but also to health-care providers.

For many years, dopamine receptor antagonists have been recommended as first choice treatment for tics, although these drugs are often associated with significant adverse effects. In Germany and several other countries, however, only haloperidol is officially licensed for the treatment of TS (5). Therefore, a large number of other substances (including clonidine, tetrabenazine, dopamine agonists, botulinum toxin, and cannabinoids) has been suggested for the treatment of tics. However, for most of these medications evidence is limited.

Data of two large recently conducted and well-powered randomized controlled trials (RCT) – including more than 100 patients each – confirmed preliminary results and demonstrated that behavioral therapy with Comprehensive Behavioral Intervention for Tics (CBIT) is an effective and safe treatment for managing the tics of children and adults with TS (6, 7). On average, CBIT treatment results in a tic improvement of about 30% [for review, see Dutta and Cavanna (8) and Verdellen et al. (9)]. CBIT is a short-term behavioral therapy consisting of only eight sessions over 10 weeks that includes psychoeducation, habit reversal training (HRT) with competing-response training (CRT), functional analysis, and relaxation training (progressive muscle relaxation). The treatment benefit of CBIT was even shown to persist over a period of 3 and 6 months (6, 7). Its effectiveness in conjunction with the lack of side effects are clear benefits of CBIT, and are advantages over currently used medications, offering thus a competitive alternative for treating tic disorders. Accordingly, in the latest guidelines – including those of the European Society for the Study of Tourette Syndrome (ESSTS) (5) – behavioral therapy with either CBIT or Exposure and Response Prevention Training (ERP) (9) is now recommended as the first-line treatment for tic disorders (10).

However in Germany and most other European countries, this recommendation cannot be implemented, since there is a considerable lack of psychotherapists trained in CBIT. Motivated by these significant barriers to dissemination, a recent study compared the effect of face-to-face to video-delivered CBIT demonstrating comparable efficacy and acceptability (11). However, while video-delivered CBIT – compared to face-to-face CBIT – is independent of the location, it is still dependent on the availability of well-trained therapists conducting the video sessions. Unfortunately, this is not the case in many European countries, including Germany, where therapists trained and experienced in CBIT are lacking on a national scale. As of today, there is even no therapy manual or patient workbook available for the treatment of adult patients with TS in German language.

In other psychiatric conditions such as depression (12, 13) and anxiety disorders (14), Internet-delivered self-guided psychotherapy (using cognitive behavioral therapy, interpersonal psychotherapy and psychodynamic treatment) has been shown to be superior to a control condition and comparably effective as face-to-face psychotherapy (15). Due to the simple nature of the exercises involved in CBIT, we have reason to assume that CBIT is particularly well suited to be delivered *via* Internet compared to those more complex psychotherapeutic interventions. Accordingly, in a recently published meta-analysis on behavior therapy for TS, the authors stated that “a major barrier to wider implementation of CBIT and HRT is that few therapists are trained in their use” and concluded that “broader distribution of behavior therapy through increased training or tele-health methods is encouraged” (16).

Therefore, the aim of this study will be to develop and test a fully self-sufficient Internet-delivered CBIT (iCBIT) for adult patients with TS, with no therapist involved in any way (ONLINE-TICS). Although interventions *via* video, Skype, or smartphone have been suggested (11, 17, 18) and, in addition, an RCT started only recently testing the efficacy of a computerized, self-administered version of CBIT (called http://TicHelper.com) in 64 children and adolescents with tics (age 8–18 years) (http://ClinicalTrials.gov Identifier: NCT02413216), to the best of our knowledge, so far, there is no iCBIT program available in any language for the treatment of tics in adult patients with TS and other chronic tic disorders. Since in TS – due to the natural waxing and waning course of tics – it is difficult to demonstrate efficacy of a treatment, only a well-designed and sufficiently powered study is suitable to demonstrate efficacy. Therefore, our study will be a multicenter, prospective, controlled, randomized, observer-blind clinical trial that aims to include 160 patients. ONLINE-TICS will be funded by the Federal Ministry of Education and Research (BMBF) in Germany (BMBF: 01KG1421). It is designed to examine the efficacy of an iCBIT intervention as compared to (1) a placebo platform consisting of psychoeducation only – which is our primary analysis – and (2) a conventional face-to-face CBIT intervention – which is our secondary analysis. We hypothesize that iCBIT (1) is superior to the placebo platform and (2) has a comparable effect size to the face-to-face treatment arm. Planned participating sites are Hannover Medical School (MHH), University of Munich, University of Aachen, University of Lübeck, and University of Dresden.

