### Eligibility Criteria

The following inclusion criteria were defined:
–chronic tic disorder or TS according to DSM-5–age ≥18 years–total tic score of the Yale Global Tic Severity Scale (YGTSS–TTS) >14 (for patients with TS and YGTSS–TTS >10 for patients with other chronic tic disorders)–CGI-S >4 at baseline–If patients receive additional medical or surgical treatment for tics and psychiatric comorbidities, they must be on a stable dose for at least 6 weeks before entering the study–fluency in German language–written informed consent.

Exclusion criteria for this study are:
–history of schizophrenia or pervasive developmental disorders–current diagnosis of substance abuse or dependence–primary comorbidities such as OCD, ADHD, depression, anxiety disorder, in need of therapy–history of behavioral treatment for tics (CBIT, HRT, ERP)–secondary tic disorders and other significant neurological and psychiatric diseases (such as schizophrenia, thought disorder)–no access to Internet or inability to operate a computer–participation in any interventional clinical study investigating drugs/medical devices 6 weeks prior to study enrollment.

These broad inclusion and exclusion criteria were based on the study by Wilhelm et al. (7), and guarantee that a representative group of TS treatment-seeking patients will be included, in particular, patients (1) with moderate or severe tics, (2) with simple or complex tics, (3) with or without comorbidities, (4) with or without additional drug treatment, (5) with short or long disease duration, and (6) of different age groups.

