### Schedule of Assessments

All clinical assessments will be performed at screening, baseline, week 5 (during treatment), week 11 (1 week after end of treatment), and 3 and 6 months after end of treatment. Follow-up assessments at 3 and 6 months after the end of treatment will provide estimates of the durability of treatment effect. Thus, time points of assessment in this study are comparable to those in the study by Wilhelm et al. (7), which recently demonstrated that face-to-face CBIT is an effective and safe intervention in adults with TS. Randomization will be performed at the baseline visit. Screening and baseline visits should not be more than 4 weeks apart, otherwise the patient will have to be rescreened. A detailed assessment schedule is provided on Table 2. At week 17 and 29 (1.5 and 4.5 months after the end of treatment), telephone visits will take place. These additional visits serve the purpose of improving compliance in order to keep the drop-out rate as low as possible. During these telephone visits there will be no further testing.

**Table 2 T2:** **Assessment schedule**.

Study period	Screening	Baseline	Treatment: (a) iCBIT, (b) placebo, (c) Face-to-face CBIT								Follow-up visits/booster-treatment^a^				
**Visit**	1	1					2				3		4		5
**Week**	−4 −0	0	1	2	3	4	5	6	8	10	11	17	23	29	35
**Treatment-session**			1	2	3	4	5	6	7	8	Frequency individual, for face-to-face CBIT: max = 2				

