#### Primary Analysis

The primary analysis will be performed in the intention-to-treat population. A mixed linear model will be used with change in YGTSS–TTS score (follow-up minus baseline) as the outcome variable. Therapy (iCBIT versus placebo), study site, concomitant tics medications (yes versus no), YGTSS–TTS baseline score, and YGTSS-TTS assessment time point (baseline, week 5, and 1 week after end of treatment) as well as an interaction of therapy and time point will be included as fixed effects in the model. The patient variable will be considered a random effect. The mixed model will be analyzed *via* PROC MIXED procedure in SAS statistical software. The therapeutic effect (iCBIT minus placebo) at week 1 after the end of treatment and the associated two-sided 95% confidence interval will be obtained from this analysis. Superiority of iCBIT will be shown if the upper limit of this confidence interval is less than 0.

Various sensitivity analyses are planned (e.g., in a per-protocol population, using analysis of covariance and more). In the unlikely event that the mixed model will not converge in the primary analysis, an analysis of covariance with last observation carried forward will be carried out instead.

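### The primary model adjusts for the baseline YGTSS-TTS only; adding the screening score already collected could modestly narrow the confidence interval (an efficiency option, not an error)

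*Protocol article*

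**What the plan says.** The Introduction of the protocol article states that "due to the natural waxing and waning course of tics – it is difficult to demonstrate efficacy of a treatment" and draws the consequence that "only a well-designed and sufficiently powered study is suitable to demonstrate efficacy".

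Under Schedule of Assessments, "All clinical assessments will be performed at screening, baseline, week 5 (during treatment), week 11 (1 week after end of treatment"; the YGTSS row of Table 2 is marked in both the screening and the baseline columns. Randomisation takes place at the baseline visit. On spacing, "Screening and baseline visits should not be more than 4 weeks apart". No minimum gap is given: Table 2 shows screening as week −4 to 0 and labels both columns Visit 1.

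Under Eligibility Criteria, one entry condition for patients with Tourette syndrome is "total tic score of the Yale Global Tic Severity Scale (YGTSS–TTS) >14", with a lower threshold for other chronic tic disorders. Table 2 places the eligibility check at screening.

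The Primary Analysis lists the covariates "study site, concomitant tics medications (yes versus no), YGTSS–TTS baseline score" and the time points "YGTSS-TTS assessment time point (baseline, week 5, and 1 week after end of treatment". The screening score is neither a covariate nor a time point. The key secondary non-inferiority comparison with face-to-face CBIT uses the same model.

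**The concern.** In a fluctuating disorder, one rating is a noisy measure of a patient's usual severity. Two ratings taken before treatment carry more information about that level, and both exist in this trial at no extra cost. The fixed covariate list uses one of them. If the screening rating predicts the week-11 score beyond what the baseline rating already predicts, leaving it out keeps avoidable variance in the residual, and the interval for iCBIT minus placebo is wider than it need be. The same holds for the comparison with the 16 face-to-face patients, where precision is scarcest. What is at stake is precision only, not bias or type I error.

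**Working it through.** **Inputs from the protocol article (Sample Size Calculation, Secondary Analyses):** difference 3.0, SD 5.5, one-sided alpha 2.5%, 72 per arm, 16 face-to-face patients, non-inferiority margin 3. It is not stated whether the SD is adjusted for baseline; here it is taken as the residual SD of the planned single-baseline model.

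**Assumed, because the documents give no correlations:** r_b (baseline with week 11), r_s (screening with week 11) and r_pre (screening with baseline).

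**Plan's own figure.** n = 2 × (1.960 + 1.282)² × (5.5/3.0)² = 70.6, so 71 per arm by the normal approximation. The noncentral t gives 72 (power 89.8% at 71, 90.2% at 72). The stated 72 reproduces. By the normal approximation, power at 72 is 90.5%.

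**Residual variance, as a fraction of the outcome variance:**
- baseline only: 1 − r_b²
- both scores as covariates: 1 − (r_b² + r_s² − 2·r_b·r_s·r_pre)/(1 − r_pre²)
- with r_b = r_s = r, the second becomes 1 − 2r²/(1 + r_pre)

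The interval width scales with the square root of the variance ratio.

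| r_b / r_s / r_pre | baseline only | both | variance cut | interval narrower by | power at 72 per arm |
|---|---|---|---|---|---|
| 0.6 / 0.54 / 0.9 | 0.640 | 0.640 | 0% | 0% | 90.5% |
| 0.6 / 0.5 / 0.8 | 0.640 | 0.639 | 0.2% | 0.1% | 90.6% |
| 0.6 / 0.5 / 0.7 | 0.640 | 0.627 | 2% | 1% | 91.1% |
| 0.6 / 0.6 / 0.8 | 0.640 | 0.600 | 6% | 3% | 92.2% |
| 0.5 / 0.5 / 0.5 | 0.750 | 0.667 | 11% | 6% | 93.5% |
| 0.6 / 0.6 / 0.6 | 0.640 | 0.550 | 14% | 7% | 94.2% |
| 0.7 / 0.7 / 0.7 | 0.510 | 0.424 | 17% | 9% | 94.9% |

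The first row is strict decay: 0.54 = 0.6 × 0.9, so the older score adds nothing once baseline is known.

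**Entry threshold and same-day visits.** Simulating the three equal-correlation rows with screening truncated at >14 (assumed mean 24, SD 7) gives variance cuts of 9%, 12% and 15%, so the interval narrows by at most about 8%. If 30% of patients (assumed) also have both ratings on one day, the cuts are 6%, 8% and 10%.

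**Averaging instead of adding a covariate.** With 0.6 / 0.5 and r_pre 0.7–0.8, the mean of the two ratings raises residual variance by 0.6–4% and power becomes 89.5–90.4%. A separate covariate avoids this because the model estimates its weight.

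**Face-to-face comparison** (72 versus 16, ignoring the further loss from site adjustment with that arm at one site only). SE = 5.5 × √(1/72 + 1/16) = 1.52; 95% half-width = 1.96 × 1.52 = 2.98, against the margin of 3. Power at a true difference of zero is about 51%. A 6% variance cut gives a half-width of 2.89 and power of 53%; a 15% cut gives 2.75 and 57%.

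**The case against.** The strongest reply is that nothing here is wrong. Adjusting for the score at the randomisation visit is standard, matches a change-from-baseline response and is unbiased under randomisation, and the planned sample size reaches its stated power. That stands.

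A reader might infer that the protocol calls fluctuation the main obstacle and then throws away data that would remove it. The documents do not support this:
- The Introduction says only that fluctuation makes efficacy hard to show. It does not rank obstacles, and it answers with design quality and power.
- The screening rating has an evident purpose, since a YGTSS-TTS threshold is an entry criterion and eligibility is checked at screening. That it serves no other purpose is an inference; the article leaves its list of sensitivity analyses open.
- A noise reduction is possible but not established. If ratings closer in time correlate more, as waxing and waning suggests, the older rating adds 0–2%. The counter-argument, that patients fluctuate around a stable personal level, gives more, but it too is an assumption.
- With no minimum gap, the two ratings need not form a run-in. Entering one score twice for same-day patients also imposes the same coefficients on patients with one rating and patients with two, which dilutes the gain.

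For the face-to-face arm, the article already says that this comparison is not powered, and the change would not alter that. These points shrink the benefit. None shows harm from a second pre-randomisation covariate beyond one degree of freedom.

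**Conclusion.** The point holds as a modest, nearly free efficiency improvement, not as an error or a contradiction. The residual variance of the week-11 contrast would fall by between 0 and about 17%, and the confidence interval would narrow by about 0–8% (9% only if all ratings correlate 0.7 and truncation at entry is ignored). Power at 72 per arm would move from 90.5% to between 90.5% and about 95%. Where in that range the trial falls depends on correlations, visit spacing and the share of same-day visits, none of which the documents give. No pre-treatment rating can remove fluctuation in the week-11 score itself.

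**What to change.** Before unblinding, add the screening YGTSS-TTS to the fixed effects listed under Primary Analysis, beside the baseline score, and carry it into the key secondary non-inferiority model. Keep change from the baseline visit as the response. Enter the two scores separately and do not average them. Where screening and baseline fall on the same day, use the single score for both and say so in the plan. The cost is one degree of freedom and one extra term in the model statement; no new visits, data or patients are needed. The gain may turn out to be nil, so the sample size should not be reduced on the strength of it.

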## Methods and Analysis

### Study Sample

Over the course of 2 years, 160 patients will be enrolled in this study. The recruitment will run primarily through the study centers’ outpatient clinics. Moreover, further advertisement will be carried out by German self-help and advocacy groups, newsletters, and annual meetings. Patients who are interested in participation will be referred to the study centers, where they will be informed about the details of the study and an appointment for a screening visit will be made.

During screening, patients will be informed (orally and in writing) about clinical assessments and randomized allocation. Those patients who will not be randomized to iCBIT during the RCT, will have the opportunity of receiving iCBIT after study completion (i.e., after their follow-up assessments). There will be no financial compensation for the study participation. However, travel costs will be reimbursed. Before being enrolled, patients will have to provide written consent. We expect a screening rate of 280 patients in 2 years, out of which about 240 patients are expected to meet the inclusion criteria for this study, out of which 160 should be willing to participate and will be included. Planned recruitment by study site is displayed on Table 1.

**Table 1 T1:** **Numbers of patients approximately recruited per center**.

	Center	Principal investigator	Expected *n* of patients recruited for the complete trial
1	Hannover Medical School	[name]	62
2	Ludwig-Maximilians-University Munich	[name]	28
3	University of Lübeck	[name]	24
4	University Hospital Aachen	[name]	26
5	University of Dresden	[name]	20
	Total		160

*n, number*.

### Study Design

This is a multicenter, prospective, randomized, controlled, observer-blind clinical trial on the efficacy of iCBIT in the treatment of tics in adult patients with TS or other chronic tic disorders. For four of the five planned study sites (except for Hanover), a two-armed study design will be used – consisting of a placebo-treatment arm (Internet-based psychoeducation) and an iCBIT-treatment arm. Only in Hannover (MHH), an additional face-to-face CBIT treatment arm will be added. Hannover is the only center offering the face-to-face treatment due to the lack of well-trained therapists in Germany even in centers specializing in TS.

The time from first patient in to last patient out is expected to be 33 months consisting of the recruitment phase (24 months) plus the treatment phase (10 weeks) plus a follow-up (6 months). The drop-out rate is expected to be less than 10%.

This study is registered on ClinicalTrials.gov Identifier: NCT02605902.

